### Economic evaluation

An economic evaluation will be conducted alongside the RCT to estimate the cost and cost-effectiveness of the intervention versus the control; analyses will be based on intention-to-treat (ITT) in line with the statistical analysis. We will estimate the cost-effectiveness of the intervention based upon the primary effectiveness outcome (severe illness or death in infants in the first 3 months of life). We will use a societal perspective and include a broad range of costs including (but not only) out-of-pocket costs on antibiotics by the household. The resources used to deliver the intervention are collected from the study sites using a micro-costing approach and the Cost of Integrated Newborn Care (COIN) framework and include set up and training costs so that policy-makers are aware of the resource implications of adopting this intervention. Face-to-face standardised questionnaires are used to collect information on socio-economic status of households and health-seeking behaviour and health resource utilisation at baseline and 3 months. A regression model will be used to adjust for systematic differences between intervention and placebo arms at baseline and will be used to calculate the incremental cost-effectiveness ratio (ICER) for the primary outcome measure. A bootstrap procedure to estimate the confidence intervals of the ICER estimates and cost-effectiveness acceptability curves will be used to describe the likelihood of cost-effectiveness at different cost-effectiveness thresholds from WHO [18, 19]. The robustness of the results will be assessed through one-way sensitivity analyses and by using a Tornado diagram to show the greatest sources of uncertainty. All prices in Ugandan shillings will be exchanged to Purchasing Power Parity US dollars in order to allow international comparability.

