#### Intervention arm

Women in the intervention arm receive all the comparator arm interventions as above. In addition, they receive a total of six litres of ABHR: a full 1-litre dispenser for use at home and an empty 60 ml-bottle for use outside of the house) and a 5-litre container for refill (Picture 2).

When the ABHR is delivered, each household obtains training on the correct use of ABHR in late pregnancy and postnatal. This is repeated at fortnightly meetings, face-to-face, or by telephone, until the participant gives birth (Table 1). During the scheduled visits, the trainer measures the amount of remaining ABHR in order to monitor usage and counsels the participant if ABHR is being underused or overused. Implementing provision of ABHR will not require alteration to usual care pathways and these will continue for both trial arms. We will discontinue the ABHR if the participant develops a reaction to the product or requests to opt out.

**Table 1 Tab1:** Participant’s timeline with study procedures conducted by research midwife (RM) for recruitment and follow-up and by the ABHR trainer

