#### Randomisation

The randomisation process was conducted in each of the three hubs separately and in the presence of representatives from each village within that geographical area. The clusters in each area were listed in order of their population size. The four clusters with the largest populations were labelled “stratum 1”, the next four largest as “stratum 2”, and so on down to the four smallest size clusters (stratum 6). Two red and two yellow balls were put in an opaque cotton bag. The representatives from stratum 1 were called forward and each in turn blindly withdrew one ball without replacement. This process was repeated for the remaining five strata in turn to randomly designate 12 clusters as “red” and 12 as “yellow”. Finally, just one red and one yellow ball were placed in the bag and the eldest of the representatives present asked to blindly withdraw one ball. The clusters designated to the colour of the chosen ball were allocated to the intervention arm of the study and the clusters designated to the colour undrawn were allocated to the comparator arm of the study. The randomisation was thus stratified by geographical area and by population size. [name], a researcher not involved in the day-to-day running of the trial has, kept the final randomisation sequence and will only avail this to the other scientists at the end of trial.

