### Statistical methods

#### Size determination

The total sample size for this study is 5932 mothers and their babies (multiple births were considered to be a single birth for this calculation). The sample will be obtained from 72 clusters arranged in 3 geographical areas of 24 clusters. The intra-cluster coefficient (ICC) estimate from the pilot study was 0.17 (95% CI 0 − 0.65); however, a study by Pagel [17] reported ICC estimates from five similar context cluster-randomised trials predominantly in the range 0.01 to 0.10, which is considered more realistic for the proposed study. The sample size calculations are based on a primary endpoint of severe infection, with estimated rates of 5–30%.

The anticipated sample size will have:90% power to detect a reduction in infection rate of ≥ 25% for comparator arm rates down to 15% if ICC ≤ 0.01, or to detect a reduction in infection rate of ≥ 33% for comparator arm rates down to 5% if ICC ≤ 0.001.80% power to detect a reduction in infection rate of ≥ 25% for comparator arm rates down to 10% if ICC ≤ 0.01, or to detect a reduction in infection rate of ≥ 33% for comparator arm rates down to 5% if ICC ≤ 0.005.

In the pilot study, we had a small (2%) loss to follow-up rate. Therefore, only complete cases will be used with no imputation of missing outcomes. No adjustment of sample size is planned for such a small rate of loss to follow-up, but the rate is being monitored by the ISDMC so that the final recruitment time can be extended if needed.

Clusters that reach their planned sample size early will continue to recruit until the study recruitment period is completed. If the planned recruitment size is not achieved by the end of the planned time period, the study may be underpowered, in which case permission will be sought from the management committees and funder to continue recruiting for a longer period to reach the required sample size.

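### The bootstrap confidence interval for the ICER is not limited to the case where the effect is clearly above zero; otherwise, an interval ranked on the ratio cannot be read

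*Protocol article*

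**What the plan says.** The Economic evaluation section of the protocol article describes a regression model that "will be used to calculate the incremental cost-effectiveness ratio (ICER) for the primary outcome measure". The denominator is therefore the between-arm difference in severe illness or death by 3 months. For uncertainty it plans two summaries in one sentence. The first is "A bootstrap procedure to estimate the confidence intervals of the ICER estimates". The second is that "cost-effectiveness acceptability curves will be used to describe the likelihood of cost-effectiveness at different cost-effectiveness thresholds from WHO". The section names no interval type and no rule for ordering the replicates. It does not say what is reported if the effect is near or below zero, and it does not mention net monetary benefit or the cost-effectiveness plane.

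Two other sections bear on how often the problem would arise. Under Size determination, the ICC from similar trials is given as "predominantly in the range 0.01 to 0.10, which is considered more realistic for the proposed study", and comparator rates of 5 to 30% are considered. Under Intervention arm, "Women in the intervention arm receive all the comparator arm interventions as above", with six litres of hand rub and repeated training on top. A positive incremental cost is therefore likely, but no amount is given.

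**The concern.** Write the ICER as dC/dE, where dC is the extra cost and dE the events averted. The ratio orders results sensibly only while dE keeps one sign. Take dC = 10 and dE = -0.025 (dearer and harmful): the ratio is -400. Take dC = -10 and dE = +0.025 (cheaper and beneficial): the ratio is again -400. Near dE = 0 the ratio jumps between very large positive and very large negative values. Once the replicates lie on both sides of zero effect, the 2.5th and 97.5th centiles of the ratio are not the ends of a range from good to poor value. With a positive dC, the replicates that show harm at extra cost sort to the low end, which normally means best value.

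The section names policy-makers as an audience. A negative lower limit invites them to read that the intervention may save money when the replicates behind it show possible harm at extra cost.

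**Working it through.** **Inputs.** From Size determination: "The total sample size for this study is 5932 mothers and their babies" and "The sample will be obtained from 72 clusters arranged in 3 geographical areas of 24 clusters". From Randomisation: equal allocation within each area ("to randomly designate 12 clusters as “red” and 12 as “yellow"). Hence 36 clusters and 2966 mothers per arm, with mean cluster size m = 5932/72 = 82.4. Comparator rates (5 to 30%), the 25% reduction and the ICC range 0.01 to 0.10 are also from Size determination. Assumed: two-sided 5% level, because the article states none for the sample size; normal approximation; a bootstrap that reflects the clustering; and a clearly positive dC.

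**The plan's own figure.** No figure is given for the ICER. The nearest is the power statement of 80% for a 25% reduction at a 10% rate and ICC 0.01.
- Design effect = 1 + (82.4 - 1) x 0.01 = 1.81.
- SE(dE) = sqrt(1.81 x (0.10 x 0.90 + 0.075 x 0.925)/2966) = 0.0099.
- z = 0.025/0.0099 = 2.53.
- Power = Phi(2.53 - 1.96) = 0.716.

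This falls short of 80%. A one-sided 5% test gives 81.2%, but the article states no such test. That shortfall is a separate matter; what is used here is the SE.

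**When the ICER interval fails.** With dC clearly positive, the lower limit of a ratio-ranked 95% interval turns negative when more than 2.5% of replicates have dE < 0. That is when the lower 95% limit of dE is below zero. The share of trials in which this happens is Phi(1.96 - z). For a true 25% reduction:

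| Comparator rate | dE | ICC | Design effect | SE(dE) | z | Share of trials |
|---|---|---|---|---|---|---|
| 10% | 0.025 | 0.01 | 1.81 | 0.0099 | 2.53 | 28% |
| 10% | 0.025 | 0.05 | 5.07 | 0.0165 | 1.52 | 67% |
| 10% | 0.025 | 0.10 | 9.14 | 0.0222 | 1.13 | 80% |
| 15% | 0.0375 | 0.01 | 1.81 | 0.0118 | 3.18 | 11% |
| 15% | 0.0375 | 0.05 | 5.07 | 0.0197 | 1.90 | 52% |
| 15% | 0.0375 | 0.10 | 9.14 | 0.0265 | 1.42 | 71% |
| 30% | 0.075 | 0.01 | 1.81 | 0.0153 | 4.89 | 0.2% |
| 30% | 0.075 | 0.10 | 9.14 | 0.0344 | 2.18 | 41% |

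At a 5% rate and ICC 0.01 the share is 58%.

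**Check by simulation.** With an assumed cost difference of 10 (SE 1), a 10% rate, a 25% reduction and ICC 0.01, 4000 simulated trials of 2000 replicates gave a negative lower limit in 27.9%, in line with 28%.

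**What the interval looks like.** Assume a cost difference of 20 (SE 3) and let the trial's estimate equal the true 25% reduction.
- 15% rate, ICC 0.01: 0.1% of replicates have dE < 0; interval 293 to 1409, readable.
- 10% rate, ICC 0.01: 0.6%; interval 394 to 3090, readable.
- 15% rate, ICC 0.05: 2.9%; interval -1276 to 3462.
- 10% rate, ICC 0.05: 6.4%; interval -5032 to 6870.

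In the last two cases every replicate in the lowest 2.5% is harm at extra cost.

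**Sensitivity to the cost.** At the 10% rate with ICC 0.01 and a cost difference of 10, raising its SE from 1 to 5 gives a negative lower limit in about 67% of trials. Only about half of the lowest replicates are then harm; the rest are real savings. With a net saving (-10, SE 1), none of the lowest replicates is harm at extra cost.

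**The case against.** The strongest reply is that the article does not say that replicates will be sorted by the raw ratio. A bootstrap ICER interval can be built by ordering replicates on the cost-effectiveness plane. A condensed article may also leave the construction to a fuller protocol or a health-economic plan. This stands in part: ranking by the ratio is an inference, and a reader should not conclude that the plan is bound to rank harm as favourable. It does not remove the point. The article itself chooses an interval on the ICER as a summary, with no condition on the denominator. A ratio whose denominator spans zero has no finite, ordered range, and moving from a percentile interval to another interval ranked on the ratio does not change that.

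Three further objections also stand.
- The failure is conditional. At a 10% rate, a 25% reduction and ICC 0.01, the interval is readable in 72% of trials; at a 30% rate, in nearly all.
- The harm-at-extra-cost mechanism needs a positive incremental cost. The societal perspective counts household costs, so illness averted could offset the cost of the hand rub.
- The acceptability curves can be computed from net benefit on the same replicates and do not suffer from the ordering problem. A reader might infer that the whole statement of economic uncertainty would be wrong; the documents do not support that.

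**Conclusion.** The point holds in a limited form. The plan commits to a confidence interval for the ICER without restricting it to the case where the effect is clearly above zero. If it is ranked on the ratio, that interval cannot be read once more than about 2.5% of replicates fall at or below zero effect. Over the ICC range that the protocol calls more realistic, and for a true 25% reduction, this is a foreseeable result: 28 to 80% of trials at a 10% comparator rate, 11 to 71% at 15%, and 0.2 to 41% at 30%. The shares rest on the normal approximation, equal cluster sizes and a clearly positive incremental cost. They would be larger for a smaller true effect.

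The fault lies in one of two planned summaries of a secondary, economic analysis. The point ICER, the acceptability curves and the primary effectiveness analysis are untouched.

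**What to change.** In the Economic evaluation section, replace the unconditional ICER interval with wording such as: uncertainty will be summarised, from one set of bootstrap replicates, by the incremental net monetary benefit with its 95% interval over a stated range of willingness to pay per event averted, by a plot of the replicates on the cost-effectiveness plane, and by the acceptability curve. The point ICER will be reported, and an interval for it only if the replicates do not cross zero effect.

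Net monetary benefit is lambda x dE - dC, where lambda is the willingness to pay per event averted. It is linear in both differences, so its interval stays ordered whatever their signs. No new data and no further resampling are needed. There are two small costs. The range of lambda must be stated, since the article refers to WHO thresholds without giving values per event averted. And no ICER interval appears when the effect is uncertain.

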### Quality assurance procedures

The study is monitored (by the Sponsor) in accordance with the current approved protocol, GCP, relevant regulations, and standard operating procedures. Monitoring occurs once a year. Concise SOPs for each of the study procedures are present. The REDCap data collection system includes a facility to prevent the input of incorrect data and to check unlikely data values.

### Participant and public involvement

We involved the women, families, and the public from the participating sites in the study design and continue to engage them in the conduct of the BabyGel trial. A participant and public involvement (PPI) steering team oversees all aspects of PPI in the project, including study design, trial information, protocol, and data collection tools or any other study specific documents, analysis, reporting, and dissemination. They also provide oversight for the conduct of PPI design workshops or group discussions with participants, mothers, caregivers, husbands, and clinicians.

We set up a community advisory board of 10 members at each hub. These comprise a pastor, imam, local council representative, facility in charge, a facility midwife, a private clinic representative, a mothers’ representative, father representative, a school teacher, mother-in-law, and elderly woman. These meet quarterly and discuss the project, review study protocol, documents, plans, questionnaire, progress, and interpret study outcomes.

The PPI steering team has established a specific local PPI groups at each hub, namely;Budaka hub: the sick mother/ baby group in the intervention arm,Busiu hub: the sick mother/baby group in the comparator armKolonyi hub: Non-study participants with sick-babies or sick mothers themselves

These serve as local maternal and infant infection support groups in the area. At each time, the composition is about 10 members. These groups provide a forum through which the trial team can engage with users and ensure responsive feedback. The feedback from these groups is communicated to the site trial management team (site TMT), the international trial management group (TMG), and trial steering committee (TSC).

### Trial management

The study has four oversight committees:

Trial management group (TMG)

This group consists of the CI (as the chair), study statistician, programme manager, GHTU manager, and work package leads, together with representatives from the partner organisations. This group takes responsibility for the day-to-day operational issues in delivering this study to time and target. The group meets at least once monthly in accordance with the TMG charter at which hubs will summarise progress and challenges and bring up for discussion any difficulties, as well as discuss and decide matters of general importance for the trial. Due to geographic distances between the partner organisation meet via zoom but the group tries to meet face-to-face at least once per year around the time of a national or an international conference or other meeting. All decisions regarding the overall running of the trial are made in this forum with the exception of matters of fundamental importance to the viability of the trial or that require major changes to the protocol. These will be referred to the trial steering committee (TSC).

b)Trial steering committee (TSC)

This group has overall executive decision-making powers in relation to running of the study and has strategic responsibility for the study in line with its charter. The group consists of three members completely independent to the study together with two members, the CI and the study statistician, together with the sponsor’s representative. Due to geographic distances between the partner organisations, this meeting will be via teleconference/SKYPE, but the group will try to meet face-to-face at least once during the study. A charter will be developed to describe the functioning of the TSC.

iii)Independent Safety and Data Monitoring Committee (IDMC)

The committee (ISDMC) comprises one neonatal clinical trials-experienced clinician, one hand hygiene research experienced public health expert, one health economist, and a statistician, none of whom have direct involvement with the study. The IDMC reports to the TSC. The main responsibilities of this committee is to safeguard the interests of trial participants, potential participants, investigators, and sponsor, to assess the safety and efficacy of the trial’s intervention, to monitor the trial’s overall conduct, and to protect its validity and credibility.

iv)Trial management team (TMT)

This group meets monthly and is chaired by the principal investigator or co-principal investigator at the site. The group discusses issues related to the progress of the trial at the site, and to ensure that the trial is running well.

### Dissemination

The results from the various work packages will be published as soon as possible. All papers will be submitted to high-level open access health journals. The Uniform Requirements for Manuscripts Submitted to Biomedical Journals (http://www.icmje.org/) and the CONSORT checklist for cluster-randomised trials will be used to assist with clear reporting. The trial management group forms the basis of the writing committee for the main study and gives advice on the publication and authorship of all other publications. Local dissemination meetings will be held in Kampala, Mbale, and Budaka for policy-makers and staff and in Mbale and Budaka districts for the public including local participants in the study.

## Discussion

We are evaluating whether the provision of alcohol-based hand rub (ABHR) to pregnant women for postnatal household use is effective for the prevention of severe illness or death during the first 3 months after birth. To the best of our knowledge, this is the first study that determines the effectiveness of ABHR given to mothers in preventing infant infections. Our intervention has high potential for scale-up as the ABHR can be added to birth kits that are routinely given to pregnant women. Furthermore, ABHR used in this trial was locally manufactured from a sugar processing plant and is therefore financially sustainable. The COVID-19 pandemic normalised the use of ABHR also among persons who previously showed scepticism given the alcoholic nature of the product.

Unlike previous trials in LICs that assessed whether provision of pit-latrines and hand washing facilities reduces infections, our study assessed a more proximal intervention; as the use of ABHR before touching the infant could prevent transfer of infections to the infant whether or not the family has a pit latrine. ABHR potentially reduces the inconveniences encountered in implementing hand hygiene in complex household situations where water is often scarce. Also, in places where hand washing is not feasible, practical or convenient such as funerals, parties, and while travelling, ABHR is preferable.

The large size of the trial reduces the likelihood of a type II error. The main study outcome is validated by a group of three medical doctors (a neonatologist, a paediatrician and a general doctor) and as such the likelihood of measurement bias is reduced. Also, since our definition of sepsis involves hospitalisation or death, which are hard outcomes, we reduce the potential of measurement bias since some of the signs and symptoms of child infections are non-specific.

Regular visits by trained midwives will most likely reduce the incidence of infection and death, due to early detection of poor practices or signs of infection and initiating the necessary referral. Also, the availability of study doctors and medication ensures that participants in the trial get superior care to the rest of the infants. Finally, COVID-19 normalised ABHR use; as such, participants in the control villages could use it as measure against COVID-19. We collect data on its use in both arms and will do a per-protocol analysis to assess this effect.

## Trial status

Recruitment started on 11 January 2021 and is on-going. Anticipated completion date is April 2024.

## Abbreviations

CI: Confidence interval
ABHR: Alcohol-based hand rub
AEs: Adverse events
COIN: Cost of Integrated Newborn Care
COVID-19: Coronavirus disease 2019
CRF: Case report form
GEE: Generalised estimation equations
HC: Health centre
ICC: Intra-cluster coefficient
ICER: Incremental cost-effectiveness ratio
IRB: Institutional Review Board
IRR: Incidence rate ratios
ISDMC: Independent Safety and Data Monitoring Committee
ITT: Intention-to-treat
LIC: Low-income countries
PPI: Participant and public involvement
RCT: Randomised controlled study
SAE: Serious adverse event
SD: Standard deviation
Site TMT: Site trial management team
TMG: The international trial management group
TSC: Trial steering committee
VHT: Village health team
WHO: World Health Organization
